## Abstract

**Background:**

Sepsis contributes significantly to morbidity and mortality globally. In Australia, 20,000 develop sepsis every year, resulting in 5,000 deaths, and more than AUD$846 million in expenditure. Prompt, appropriate antibiotic therapy is effective in improving outcomes in sepsis. Conventional culture-based methods to identify appropriate therapy have limited yield and take days to complete. Recently, nanopore technology has enabled rapid sequencing with real-time analysis of pathogen DNA. We set out to demonstrate the feasibility and diagnostic accuracy of pathogen sequencing direct from clinical samples, and estimate the impact of this approach on time to effective therapy when integrated with personalised software-guided antimicrobial dosing in children and adults on ICU with sepsis.

**Methods:**

The DIRECT study is a pilot prospective, non-randomized multicentre trial of an integrated diagnostic and therapeutic algorithm combining rapid direct pathogen sequencing and software-guided, personalised antibiotic dosing in children and adults with sepsis on ICU.

**Participants and interventions:**

DIRECT will collect microbiological and pharmacokinetic samples from approximately 200 children and adults with sepsis admitted to one of four ICUs in Brisbane. In Phase 1, we will evaluate Oxford Nanopore Technologies MinION sequencing direct from blood in 50 blood culture-proven sepsis patients recruited from consecutive patients with suspected sepsis. In Phase 2, a further 50 consecutive patients with suspected sepsis will be recruited in whom MinION sequencing will be combined with Bayesian software-guided (ID-ODS) personalised antimicrobial dosing.

**Outcome measures:**

The primary outcome is time to effective antimicrobial therapy, defined as trough drug concentrations above the MIC of the pathogen. Secondary outcomes are diagnostic accuracy of MinION sequencing from whole blood, time to pathogen identification and susceptibility testing using sequencing direct from whole blood and from positive blood culture broth.

**Discussion:**

Rapid pathogen sequencing coupled with antimicrobial dosing software has great potential to overcome the limitations of conventional diagnostics which often result in prolonged inappropriate antimicrobial therapy. Reduced time to optimal antimicrobial therapy may reduce sepsis mortality and ICU length of stay. This pilot study will yield key feasibility data to inform further, urgently needed sepsis studies. Phase 2 of the trial protocol is registered with the ANZCTR (ACTRN12620001122943).

**Trial registration:**

Registered with the Australia New Zealand Clinical Trials Registry Number ACTRN12620001122943

## Introduction

Sepsis contributes significantly to morbidity and mortality of children and adults worldwide with an incidence that is increasing in line with global estimates ([name] et al., 2015; Fleischmann-Struzek et al., 2018; Rudd et al., 2020). Close to 20,000 Australians develop sepsis every year, in whom approximately 5,000 deaths occur. The cost to the Australian healthcare system has been estimated to exceed AUD$846 million annually, with ICU treatment required for ongoing organ dysfunction resulting in the majority of costs (https://www.georgeinstitute.org/sites/default/files/documents/stopping-sepsis-national-action-plan.pdf). Appropriate antibiotic therapy is demonstrably effective in improving outcomes in sepsis (Kumar et al., 2009; Seymour et al., 2017; Levy et al., 2018; Evans et al., 2018). However, the appropriateness of antibiotic therapy in sepsis is still predominantly determined by traditional susceptibility testing of cultured organisms. These conventional techniques have a yield below 50% in most ICU studies and take days to complete (Agyeman et al., 2017). It is often 48 to 72 hours before antibiotic susceptibility of pathogens are known, leading to substantial delays in optimizing antibiotic therapy, and to overuse of broad spectrum antibiotics. This timeframe for the identification of a causative organism and its susceptibility profile may result in a prolonged period of inappropriate empirical treatment. In an era of increasing antibiotic resistance, such suboptimal therapy can contribute to increased resistance, and worse patient-centred outcomes. In adults, it has been observed that Gram-negative healthcare-associated infections are associated with significant delays in effective antibiotic therapy. Such delays prolong the requirement for intensive care and lead to increased morbidity, mortality and cost (Moehring et al., 2013). A day in ICU costs approximatively AUD$6,000 for ICU infrastructure alone. Hence strategies with the potential to hasten patient recovery and shorten ICU length of stay have great promise to be cost-effective.

A rapid, sensitive technique capable of identifying the pathogen responsible for sepsis, along with its susceptibility profile has the potential to substantially improve clinical outcomes through earlier selection of effective antimicrobial therapy. Culture-independent methods which are not limited to specific pathogen targets are appealing. Sequencing-based approaches meet these requirements. In particular, the Oxford Nanopore Technologies (ONT) MinION device provides informative sequence data in real-time (Clarke et al., 2009), offering the potential for rapid pathogen identification along with susceptibility profiles. This effectiveness can be maximised by optimising antibiotic concentrations through individualized dosing ([name] et al., 2014; Abdul-Aziz et al., 2020).

We propose an integrated approach to personalize antimicrobial therapy in children and adults with sepsis. We will evaluate the impact of portable nanopore sequencing using the ONT MinION device integrated with Bayesian dosing software (ID-ODS) to ensure achievement of maximally effective personalised antibiotic exposures in critically ill children and adults with sepsis.

## Trial Design

The DIRECT study is a pilot prospective, non-randomised multicentre trial of an integrated diagnostic and therapeutic algorithm combining rapid direct pathogen sequencing and software-guided, personalised antibiotic dosing in children and adults with sepsis on ICU. It includes a diagnostic accuracy study of real-time pathogen sequencing direct from patient blood using the ONT MinION device, which will be compared to conventional pathogen sequencing of cultured isolates, and conventional blood culture and phenotypic susceptibility testing. This study protocol follows the Standard Protocol Items: Recommendations for Interventional Trials (SPIRIT) guidelines (Chan et al., 2013). See **Supplementary File 1**.

## Hypothesis

Real-time pathogen sequencing combined with dosing software to identify optimised personalised antimicrobial therapy will reduce the time to effective antimicrobial concentrations in critically ill patients with sepsis leading to improved patient outcomes.

## Aim

To demonstrate the feasibility and diagnostic accuracy of real-time pathogen sequencing direct from clinical samples and estimate the impact of this diagnostic approach on time to effective therapy when integrated with personalised antimicrobial dosing in children and adults on ICU with sepsis.

## Objectives

### Primary Objective

To estimate the reduction in time to effective antibiotic therapy in children and adults with sepsis using rapid pathogen sequencing combined with dosing software when compared to conventional diagnostic and therapeutic regimens.

### Secondary Objectives

i. A demonstration of the feasibility of real-time pathogen sequencing in whole blood samples from critically ill children and adults with sepsis.ii. An evaluation of the diagnostic accuracy of real-time pathogen sequencing from positive blood cultures taken from critically ill children and adults with sepsis.iii. An evaluation of the time to pathogen identification comparing direct sequencing versus conventional blood cultures taken from critically ill children and adults with sepsis.iv. An improvement in the achievement of therapeutic antibiotic concentrations in patients using dosing software versus traditional dosing regimens.

## Methods

### Study Setting

The study will be undertaken in the following participating ICUs in Brisbane, Australia: Royal Brisbane and Women’s Hospital, The Prince Charles Hospital, Princess Alexandra Hospital, Queensland Children’s Hospital.

### Eligibility Criteria

Patients with suspected sepsis or septic shock admitted to participating ICUs with an onset of less than 24hours. A summary of all inclusion and exclusion criteria for participants are provided in **Table 1**.

**Table 1 T1:** Inclusion and exclusion criteria for the DIRECT study.

**Inclusion criteria** Age >1month Admitted to paediatric or adult ICU at one of the participating centres Decision to treat for suspected sepsis, defined as suspected or proven infection with or without confirmed organ dysfunction. Commenced within 24h on intravenous broad-spectrum antibiotics, or within 24h of a change to new antibiotics consistent with treatment for a new episode of suspected sepsis. Blood cultures are being obtained or were obtained within the past 12 hours
**Exclusion criteria:** Inability to gain informed consent during the study period Neonates Death is likely imminent Palliative care patient Renal replacement therapy Extra-corporeal membrane oxygenation

### Interventions

Diagnostic accuracy of MinION nanopore pathogen sequencing will be compared with conventional blood cultures and antimicrobial susceptibility testing. Acknowledging the limited yield of blood cultures in sepsis, a composite reference standard for sepsis will be used. This composite reference standard will incorporate blood culture results, other significant microbiological samples taken at the discretion of the clinical team and clinical and epidemiological features. These composite features will be interpreted independently by two experts in microbiology and infectious disease. In the event of discordance a third expert opinion will adjudicate. Complete reference genomes for matching pathogen isolates will be analysed to evaluate the differences between nanopore direct sequencing and cultured pathogens sequenced conventionally.

### Outcomes

#### Primary Outcome

The primary outcome is time to effective antimicrobial therapy defined as trough drug concentrations above the MIC of the pathogen.

#### Secondary Outcomes

Secondary outcomes are:
1) Diagnostic accuracy of MinION nanopore pathogen sequencing direct from whole blood

2) Time to pathogen identification and susceptibility testing using MinION nanopore pathogen sequencing 

a) direct from whole blood 

b) from positive blood culture broth. 

3) Evaluation of direct MinION nanopore pathogen sequencing predictive capabilities using complete reference genomes from positive blood culture broth.

#### Sample Size and Recruitment

The study will be undertaken in two phases (**Figure 1**). Phase 1 will seek to demonstrate the validity of the sequencing method applied to patients with blood culture-confirmed sepsis (n=50). Recruitment of 50 blood culture confirmed-sepsis patients in this phase is anticipated to require the recruitment of approximately 150 patients with suspected sepsis. Phase 2 will then apply these methods to consecutive patients (n=50) admitted to intensive care with suspected sepsis. No randomization of patients will occur. Recruitment to the study commenced 17th March 2020 and will be completed by 30^th^ September 2021. Education sessions were conducted with research groups from each ICU in advance of the study onset, including individual sessions with local research coordinators. Study sample packs, and flow diagrams to aid recruitment were created for participating ICUs. Research coordinators are responsible for screening potentially eligible patients with suspected sepsis on a daily basis. Finally, ethical approval was sought to recruit patients with suspected sepsis on a “consent to continue” basis, reflecting the time-critical nature of sepsis and the importance of obtaining timely research samples.

**Figure 1 f1:**
[figure not shown]
Study flow diagram. Phase 1: In an initial observational phase of the study, participants will be recruited to a diagnostic accuracy study of MinION nanopore pathogen sequencing. The sample size for this phase of the study is 50 patients with blood culture-confirmed sepsis admitted to ICU. Phase 2: In Phase 2, consecutive patients with suspected sepsis admitted to ICU will undergo MinION nanopore pathogen sequencing integrated with personalised antibiotic therapy using a combination of Bayesian dosing software (ID-ODS™) and measured antibiotic plasma concentrations. A senior ICU pharmacist/clinician at each site will lead this software-guided intervention of antimicrobial dose optimisation. All dosing regimens will be checked by both the senior ICU pharmacist and attending ICU consultant prior to prescription. The final decision regarding the use of the optimised dosing of antibiotics will remain at the discretion of the attending ICU consultant. Software-guided dosing will continue until either: 1) the study antibiotic(s) have been ceased by the treating clinician, 2) the patient is discharged from ICU, 3) after 5 days of study antibiotic therapy. If antibiotic therapy is still required thereafter, dosing will be guided by the treating clinician. Adherence to dosing strategies informed by the dosing software will be supported by the use of senior ICU pharmacists trained in the use of this software-guided approach to antimicrobial dose optimisation. All dosing regimens will be checked by both the senior ICU pharmacist and attending ICU consultant prior to prescription, to ensure appropriateness and safety.

### Consent

Patients and/or carers will be approached by clinical research staff at each participating ICU and provided with written information regarding the study. A consent to continue process will be used where prospective recruitment would lead to delays in blood sampling and preclude direct comparison with blood cultures. Carers and competent patients will be provided with the opportunity to revoke their consent and have the research blood samples and data securely disposed of prior to analysis. Eligible patients and their carers will be approached to contribute residual blood samples for the evaluation of novel, rapid sepsis diagnostics (commercial and research, culture-dependent and culture-independent).

### Ethics Approval and Consent to Participate

Ethics approval has been granted by the Children’s Health Queensland Hospital and Health Service Human Research Ethics Committee (HREC) [HREC/19/QCHQ/55177]. Written informed consent will be obtained from all participants (or their parent or legal guardian). Approval was granted by the Queensland Civil and Administrative Tribunal [CRL024-19] to include patients unable to consent for themselves under the Guardianship and Administration Act 2000.

### Data Collection and Management

Clinical data on patient demographics, comorbidities, type and focus of infection, severity, clinical progress through ICU and clinical outcomes (including ICU and hospital length of stay and in-hospital mortality) will be captured by clinical research nurses into an online REDCap database hosted by The University of Queensland. Organ dysfunction in children and adults is defined in **Supplementary File 2**. In the event that a paper Case report form is used, forms will be stored in an appropriate locked storage facility with restricted access. A study ID number will be used to link de-identified clinical data with the laboratory samples. Data and samples will be retained in line with the Queensland Health Retention and Disposal Schedule and with the Australian Code for the Responsible Conduct of Research Section 2.1.1. Deidentified genome sequence data will be shared by deposition in a public nucleotide repository (GenBank and Sequence Read Archive). Adherence to the study protocol will be monitored by the Coordinating Principal Investigator, and the steering committee. Patient eligibility, consents, and sample processing will be audited every 6 months at each site. An annual progress report will be submitted to the approving human research ethics committee (HREC) and local research governance officers (RGOs). No adverse events are anticipated, and a Data Safety and Monitoring Board has not been convened.

### Study Samples

Initial study samples will be obtained during the course of the routine clinical sepsis workup. Samples will be stored until consent to participate has been sought, and will then be analysed if consent is given, or destroyed if consent is not given or revoked.

The following study samples will be obtained: i. A single study sample will be taken into an EDTA container at the time of recruitment to the study, and as close to the time of initial blood culture sampling on suspicion of sepsis. (Time=zero). Routine clinical sampling should include appropriate volumes of blood and other clinical samples for culture and susceptibility testing (**Table 2**).

**Table 2 T2:** Appropriate study sample volumes according to age, and sample type. ‘T’ is time of sampling in hours since recruitment.

Age category	EDTA (T=0)	Plasma (T=24,48,72,96h)
Infants and Young children (<5y)	1-2ml	0.5ml
Older children (5-12y)	2-6ml	1-2ml
Adolescents and adults (>12y)	6-10ml	3-5ml

The volume of blood obtained (for both children and adults) will be documented at the time of recruitment and sampling. Consent will be sought to use residual EDTA samples for the evaluation of emerging, rapid methods of bacterial detection and antimicrobial resistance identification.

ii. Plasma samples will be taken at the following time points of antibiotic therapy: at 24 hours, 48 hours, 72 hours and 96 hours post-commencement of antibiotic treatment to determine if target antibiotic plasma concentrations have been reached.

Clinical samples will be processed in line with existing laboratory requirements. Study EDTA samples will be stored at 4°C before shipping to The University of Queensland Centre for Clinical Research (UQCCR) and the Queensland Paediatric Infectious Disease (QPID) laboratory. Bacterial isolates will be stored at -80°C before shipping to UQCCR. Samples will be de-identified before shipping, and labelled with a study ID. Samples at UQCCR will be stored at -80°C until analysis.

### Reference Standard

The diagnostic accuracy of real-time pathogen sequencing using the MinION sequencer for the diagnosis of sepsis will be evaluated against a reference standard of conventional microbiological evaluation using blood culture and susceptibility testing.

### Laboratory Methods

Routine clinical samples will be processed in NATA accredited laboratories at Pathology Queensland. Time to blood culture growth, time to pathogen identification, and time to susceptibility testing completion will be collected.

### Broth Microdilution

Susceptibility testing will be undertaken at The University of Queensland Centre for Clinical Research (UQCCR) using a broth microdilution method (BMD). In house BMD plates will be made using the Hamilton Star liquid handling robot as per European Committee on Antimicrobial Susceptibility Testing (EUCAST) standards and testing will be performed on demand as isolates are made available. Antimicrobials tested by BMD will be chosen by the study investigators and will reflect available and readily used antimicrobials in clinical practice.

### Whole Genome Sequencing of Sepsis Pathogens

Bacterial cells will first be enriched using a differential lysis procedure. Residual human DNA will be degraded using a DNAse treatment, followed by nucleic acid extraction using a rapid commercial-kit based protocol. Whole genome sequencing (WGS) of sepsis pathogen isolates with ONT MinION or Illumina Miniseq instruments will be carried out at UQCCR. Bacterial isolate identity (genus, species, sequence-type) and antimicrobial resistance genotype will be determined using the Queensland Genomics Infectious Disease (QGID) clinical genomics pipeline (https://github.com/FordeGenomics/SnapperRocks). In brief, in silico taxonomic profiling of isolates will be performed by screening the sequence read data against a bacterial refseq database using Kraken2. Sequence Types will be assigned using mlst and species-specific typing schemes available on PubMLST. Acquired antibiotic resistance genes will be identified by screening the draft genomes of each isolate against the NCBI resistance gene database using abricate. Finally, intrinsic mutation associated with antibiotic resistance will be identified using Pointfinder. For both technologies, time to pathogen identification, and time to susceptibility prediction will be measured. High quality complete reference genomes will be assembled from Illumina and MinION data using the Queensland Genomics Infectious Disease (QGID) reference genome assembly pipeline, Micropipe (www.biorxiv.org/content/biorxiv/early/2021/02/03/2021.02.02.429319.full.pdf). At least one complete genome will be assembled for each species identified clinically. The complete genomes will provide a gold-standard reference to evaluate any differences between direct clinical sample sequencing and the composite reference standard.

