### ONT MinION Nanopore Sequencing

For the direct sequencing protocol, nucleic acid extracts will undergo short multiple-displacement amplification reactions followed by purification and concentration using Monarch PCR and DNA cleanup columns. The nucleic acid extract will be checked for DNA yield using a QBIT 3.0 instrument, followed by a nanopore library preparation using the ONT Rapid Sequencing Kit. The prepared sample will be loaded onto a MinION device using the R9.4.1 flow cell and run for 24 hours. Time-stamped fast5 files will be stored on UQ research data manager (RDM) for emulated real-time analysis. Taeper (https://github.com/mbhall88/taeper) will be used for emulating real-time sequencing for subsequent online analysis. The following computing steps will be carried out as a streaming pipeline based on the real-time data emulation: base-calling will be carried out using Guppy v4.0.11 run on high performance GPU (graphics processing unit) computing facilities at UQ; subsequent quality control with nanoq (https://github.com/esteinig/nanoq); species classification and identification of acquired resistance genes using JAPSA (https://github.com/mdcao/npAnalysis); and strain identification using Sketchy (https://github.com/esteinig/sketchy), for Klebsiella pneumoniae and Staphylococcus aureus identified infections. JAPSA calculates confidence intervals for the proportion of reads generated by each species identified. A species will be classified as identified if the 95% lower confidence interval of the proportion of reads from this species is greater than 0.

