### Statistical Methods

The primary outcome measure, time to optimal antimicrobial therapy will be reported by median and interquartile range. Comparison between projected time to optimal antimicrobial therapy using an integrated diagnostic sequencing and dosing algorithm will be compared with the observed time to optimal therapy using a suitable non-parametric test such as the Kruskal-Wallis test. Diagnostic accuracy of MinION nanopore pathogen sequencing will be reported as sensitivity, specificity, positive and negative likelihood ratios against the composite reference standard reported above and illustrated by a 2x2 table. Appropriate methods to handle missing data will be developed following an investigation of the pattern of missingness. Where appropriate, multiple imputation will be used to replace missing values from a distribution of plausible values.

The full protocol, patient-level dataset and statistical code will be made available on reasonable request.

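### The direct-sequencing workflow is directed at bacteria but is scored against a composite for sepsis of any cause, so one sensitivity figure may mix missed bacteria with organisms outside the assay's apparent scope

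*Protocol article*

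**What the plan says.** **Index test.** Under Whole Genome Sequencing of Sepsis Pathogens, the protocol article states that "Bacterial cells will first be enriched using a differential lysis procedure". Degradation of leftover human DNA and kit-based extraction follow. This is the only extraction described. Under ONT MinION Nanopore Sequencing, for direct sequencing, "nucleic acid extracts will undergo short multiple-displacement amplification reactions followed by purification and concentration using Monarch PCR and DNA cleanup columns". A DNA yield check and library preparation come next, and no reverse-transcription step is mentioned. The direct reads then go to "species classification and identification of acquired resistance genes using JAPSA"; the organisms covered by its reference database are not stated.

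**Reference.** The Interventions section says that "a composite reference standard for sepsis will be used". It is built from blood culture, other relevant microbiology, and clinical and epidemiological features, and is read by two experts with a third for disagreements. No limit by cause is given. The later Reference Standard section instead names conventional blood culture with susceptibility testing.

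**Population.** Table 1 admits patients treated for infection, either suspected or established, who have recently started or changed antibiotics. A bacterial cause is not required.

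**Analysis.** Statistical Methods reports sensitivity, specificity and both likelihood ratios "against the composite reference standard reported above and illustrated by a 2x2 table". The article does not say how a reference-positive fungal or viral case is scored.

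**The concern.** The index test and the target condition do not appear to have the same organism scope. The laboratory steps are directed at bacteria, while the reference concerns sepsis in general. The Introduction widens the gap by arguing that "Culture-independent methods which are not limited to specific pathogen targets are appealing".

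A false negative in the planned table could therefore mean two different things: a bacterial infection the assay failed to detect, or an infection by an organism the workflow was not set up to recover. The first is assay performance and the second is assay scope. They call for different responses in a later study, and this pilot exists to inform later studies. A single sensitivity and a single negative likelihood ratio cannot separate them.

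The exposure lies mainly among patients without a positive blood culture. Phase 1 expects about 150 suspected cases to yield 50 culture-confirmed ones, which leaves about 150 − 50 = 100 whose reference status depends on the other components of the composite. The 50 Phase 2 patients are also enrolled on suspicion.

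**Working it through.** **Figure in the plan.** The article states no expected sensitivity, specificity or precision, so there is nothing to reproduce. What follows shows the mechanism under assumed inputs.

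**Inputs**
- s = sensitivity among reference-positive patients whose organism the assay can detect. Not given; assumed 70%, 80% or 90%.
- f = share of reference-positives whose organism the assay cannot detect. Not given; assumed 5%, 10%, 20% or 30%.
- n = 50, borrowed from the Phase 1 target only to show sampling error. The number of composite-positive patients is not stated.

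**Formula.** Of N reference-positives, N(1 − f) are detectable and a proportion s of those test positive. The other Nf are taken to test negative. Apparent sensitivity = s × N(1 − f) / N = s × (1 − f).

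| s | f = 5% | f = 10% | f = 20% | f = 30% |
|---|---|---|---|---|
| 70% | 66.5% | 63% | 56% | 49% |
| 80% | 76% | 72% | 64% | 56% |
| 90% | 85.5% | 81% | 72% | 63% |

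**Negative likelihood ratio.** This is (1 − sensitivity) / specificity. For a given specificity it is multiplied by [1 − s(1 − f)] / (1 − s). At s = 80%:
- f = 5%: 0.24 / 0.20 = 1.2
- f = 10%: 0.28 / 0.20 = 1.4
- f = 20%: 0.36 / 0.20 = 1.8

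**Against sampling error.** The Wilson 95% interval for 40/50 (80%) runs from 67.0% to 88.8%. The values at f = 5% and 10% (76% and 72%) lie inside it. The value at f = 20% (64%) lies below it. The smaller shifts are within chance variation for a study of this size, although they are systematic.

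**Which organisms could count towards f**
- *RNA viruses:* only DNA steps are described, so no route to detection is stated.
- *Fungi:* uncertain. Enriching bacterial cells is not the same as removing every fungal cell, and the classifier's coverage is not given.
- *Under blood culture alone as reference:* viral sepsis would not be reference-positive, and only culture-positive fungal cases could matter. The 50 culture-confirmed Phase 1 patients are exposed only in this limited way.

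**The case against.** Several points on the other side stand.

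1. A reader might infer that the workflow can identify bacteria and nothing else. The text does not establish this. The bacterial database is stated for cultured isolates: "in silico taxonomic profiling of isolates will be performed by screening the sequence read data against a bacterial refseq database using Kraken2". The accuracy table concerns direct sequencing, which uses a different classifier of unstated coverage. The isolate database is no defect either, since that pipeline is described as serving bacterial isolates and routine laboratories process the clinical samples.
2. A reader might also infer that every non-bacterial case is bound to be a false negative. That depends on what the experts score: sepsis of any cause, bacterial infection, or a named pathogen. The article does not say, nor does it say which patients enter the table. A full protocol, which is not shown, may.
3. Sensitivity is too low only if the intended target is bacterial infection. If the target is sepsis of any cause, the lower value is the right answer to that question.
4. Requiring recent antibiotic treatment favours suspected bacterial sepsis, which makes a large f less plausible.
5. The data collected include type and focus of infection, so a breakdown could probably be made later.

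These points limit the claim but do not remove it. The composite as written has no restriction by cause, accuracy is to be computed against it, and on either choice of target one table cannot separate missed bacteria from organisms out of scope. A breakdown made after the results are known is weaker than one fixed at adjudication.

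**Conclusion.** The point holds as a mismatch of scope, conditional on the composite counting non-bacterial sepsis as positive. In that case the reported sensitivity and negative likelihood ratio mix assay performance with assay scope.

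The size cannot be derived from the documents. Sensitivity is multiplied by 1 − f, and both f and s are assumptions. At s = 80% the loss is 4 points at f = 5% and 24 points at f = 30%. This rests on undetectable cases testing negative. A spurious species call in such a patient, if scored at patient level, would reduce the apparent loss. The lack of a route is well supported for RNA viruses and unresolved for fungi.

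The documents do not support saying that the assay is blind to everything except bacteria, or that the planned sensitivity is biased whatever its target.

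**What to change.** In Interventions and Statistical Methods:

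1. Have the existing adjudicators record pathogen class for each patient: bacterial, fungal, viral, mixed or none.
2. Keep the planned table against the all-cause composite.
3. Add a prespecified table with bacterial infection as the target condition. Mixed cases with a bacterial component are target-positive. Purely fungal or viral cases are target-negative and stay in the specificity denominator; leaving them out would distort the specificity. State in advance how patients classed as none are placed.
4. Report detection of fungal and viral cases separately.

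The Reference Standard section should be reconciled with the other two, because the choice of reference decides which non-bacterial cases are exposed.

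The cost is one field on the adjudication form and one further table, with smaller numbers in each class and so wider intervals.
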